#### Outcome measurements

Measurements will be performed at the baseline (week 0), end of the intervention (week 12) and follow up (week 24).

### Primary outcomes

#### PBF

The PBF will be measured with a BIA instrument (Inbody S10, Korea), which is one of the assessment tools recommended by the AWGS 2019 owing to its noninvasive, inexpensive and easy-to-use nature and portability [27]. The participants must stand for more than 10 min before the measurement to redistribute the water inside their body, with their arms about 15º away from their trunk and feet, not barefoot, shoulder-width apart. The researcher will place eight contact electrodes on specific parts of their body (i.e. thumbs, index finger of both hands and inner and outer ankle of both lower limbs), and the participants must avoid touching any metal object other than the BIA instrument during the measurement. The BIA instrument will automatically measure the participants’ PBF.

#### Muscle strength of lower limbs

Lower limb muscle strength is reflected by the KES, which is assessed by the estimated 1RM. The standard 1RM test has exercise injury risks for older people [36]; therefore, the estimated 1RM test will be used to measure the exercise load. The exercise load will be measured in kilograms, with the participant sitting in an extensor chair equipped with a weight plate with an initial load of 45% of the body weight for women and 64% of the body weight for men [37, 38]. If the participant can perform knee extensions > 10 times with the initial weight, then the plate weight should be increased until the participant can repeat the exercise 10 times or less, at which the submaximal weight will be set as the weight of the plate. The following calculation formula will be used: estimated 1RM (kg) = submaximal weight (kg)/(1.0278—maximal repetitions*0.0278) [39].

### Secondary outcomes

#### Body composition

Body composition includes muscle mass (appendicular skeletal muscle [ASM] and ASMI) and obesity-related indicators (total fat mass [FM]). The ASM and FM will be measured directly through BIA, and the ASMI will be calculated with the following formula: ASMI (kg/m^2^) = ASM (kg)/height^2^ (m) [27].

#### Anthropometric measurements

The morphometric measurements will include the waist circumference (WC), hip circumference (HC) and waist-to-hip ratio (WHR). The researcher will measure the participant’s WC (circumference of the midpoint between the lowest rib point and upper edge of the iliac crest on a horizontal plane) and HC (the most prominent circle of the hip) whilst in a standing position, using a soft dermatome, then divide the WC by the HC to get the WHR.

#### Muscle strength of upper limbs

Changes in the upper limb muscle strength will be reflected in the HS. The measurement procedure is as follows: (1) the participant will hold a Jamar® Plus handheld grip dynamometer (Jamar Plus + Digital Hand Dynamometer; IL, USA) at a 90º elbow flexion whilst in a seated position, then (2) perform the grip on each hand three times at maximum strength. The maximum value will be recorded as the HS [27].

#### Physical performance

Physical performance will be assessed with the 6-m walk test and short physical performance battery (SPPB) test. We chose the SPPB and 6-m walk tests, because they are recommended by the AWGS 2019 [27]. In addition, a systematic review of 12 functional assessment tools for older people pointed out that the SPPB test has the highest validity, reliability and responsiveness scores [40]. For the 6-m walk test, the participants will be asked to walk 6 m at their daily GS, which will be timed by a researcher using a manual stopwatch, and the average result of at least two tests will be recorded as the final GS [27].

The SPPB test consists of three elements: the standing balance test, 4-m walk test and chair sit-to-stand test [41]. For the standing balance test, the participants will be asked to stand side by side, stand in semitandem and stand in tandem, following the researcher’s command, and the researcher will score the participants based on the duration. For the 4-m walk test, the participants will be instructed to walk 4 m at their regular walking speed. The test must be repeated and measured 2 times, and the shortest time will be recorded. For the chair sit-to-stand test, the participants must cross their arms in front of their chest whilst in a sitting position and repeat standing up and sitting down 5 times at their fastest speed. The exercise will be timed from the beginning of the sitting position to the standing position.

#### Haematological parameters and CVD risk factors

A professional nurse will collect each participant’s upper arm venous blood before the baseline (week 0), after the end of the intervention (week 12) and at the follow up (week 24). The participants will be asked to fast for 12 h before the blood collection. The blood samples will be sent to a laboratory for testing.

The following indicators will be determined via automated enzyme-linked immunosorbent assay: inflammatory factors (IL-6, CRP and TNF-α), hormones (IGF-1), growth factors (MSTN), adipose factors (LEP and ADP) and CVD risk factors (FPG, triglyceride [TG], TC, high-density lipoprotein cholesterol [HDL-C], low-density lipoprotein cholesterol [LDL-C] and FINS).

Insulin sensitivity will be expressed by the homeostasis model assessment of the IR (HOMA-IR), with a decrease in the HOMA-IR representing an increase in insulin sensitivity. The calculation formula is HOMA-IR = (FINS μU/mL*FPG mmol/L)/22.5 [42].

The other CVD risk factors (resting heart rate [HRrest], SBP and DBP) will be measured using an electronic blood pressure monitor (OMRON, U30, China).

#### Quality of life

The participants’ quality of life will be assessed using the Chinese version of the 36-item Short Form Health Survey Scale (SF-36), which has been confirmed as reliable and valid, with an overall Cronbach’s α coefficient of 0.943 and each dimension having a Cronbach’s α coefficient of > 0.70 [43, 44]. The SF-36 consists of 36 items covering eight domains (i.e. physical function, physical role, physical pain, general health, vitality, social function, emotional role and psychological health) [45]. The total score will range from 0 to 100, and the higher the score, the higher the quality of life.

#### Sample size

The sample size will be calculated using G*Power version 3.1 [46]. Clarkson et al. [47] indicated that the outcome that is most relevant to the effect of BFR is the KES; therefore, the KES will be used as the primary outcome indicator to calculate the sample size. The effect size f of the study will be determined as 0.65 based on a previous study [24]. The relevant parameters will be set, as follows: an alpha of 0.05, a power of 0.8 and an effect size of 0.65, with a total sample size of 27 participants (9 participants per group). The total sample size of the study will be set to 33 participants (11 participants per group), considering a 20% dropout rate.

### Statistical analysis

All the outcome data assessed in the study will be entered into a database via SPSS Statistics version 26 (SPSS, Inc., USA) for the statistical analysis. All the data will be expressed as the mean ± standard deviation or median. The categorical variables will be tested using the chi-square test, and comparisons between the groups will be conducted using one-way ANOVA or the Kruskal–Wallis test. The results will be described as 95% confidence intervals and regarded as significant at *P* < 0.05.

Differences in the outcomes over time between the LRE-BFR, CRE and control groups will be analysed with linear mixed models following the intention-to-treat principle. Missing data will be designated as randomly missing, and the data will be processed using maximum likelihood and linear mixed models.

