**Methods and analysis:**

This work is a 12-week assessor-blinded randomised clinical trial that will be conducted thrice a week. Sarcopenia will be defined using the Asian Working Group for Sarcopenia 2019, and obesity will be determined using the criteria developed by the World Health Organization. Community-dwelling older people aged ≥ 65 years will be screened as the participants using inclusion and exclusion criteria. A total of 33 participants will be randomised into a CRE group (*n* = 11), an LRE-BFR group (*n* = 11) and a control group that will be given only health education (*n* = 11). The primary outcomes will be knee extensor strength and PBF, and the secondary outcomes will be body composition, anthropometric measurements, muscle strength of upper limbs, physical performance, haematological parameters, CVD risk factors and quality of life. The outcomes will be measured at the baseline (week 0), end of the intervention (week 12) and follow up (week 24). All the collected data will be analysed following the intention-to-treat principle.

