Therefore, this study has the following objectives: (1) to comprehensively evaluate the efficacy of a 12-week CRE and LRE-BFR intervention in improving the body composition, muscle strength, physical performance, haematological parameters, CVD risk factors and quality of life of older people with SO and (2) to compare the efficacy of CRE and LRE-BFR and explore their potential mechanisms.

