### Randomisation and blinding

The final participants will be randomly assigned to an LRE-BFR, CRE or control group, with a 1:1:1 ratio. To ensure the allocation concealment, the randomisation sequence will be generated after the baseline assessment by a statistician who is not involved in the study, using SPSS version 26 (SPSS, Inc., USA), and stratified by gender and age to achieve a balanced distribution, with as many males and females in each group as possible. An electronic file of the random numbers and grouping will be encrypted by the statistician and sent to another external researcher to store the information. The information will be given to the therapist in a sealed envelope. All the outcome assessors, statisticians and data managers involved in this study will be blinded to the group assignment prior to the completion of the statistical analysis. Given the nature of this study, the participants and therapist cannot be blinded to the group assignment.

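### KES and PBF are unranked primary outcomes judged at the same P < 0.05, so if either may carry the trial the false primary claim rate is about 9% to 10%, not the 5% used for sizing

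*Protocol article*

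**What the plan says.** - **Two primary outcomes.** The abstract states: "The primary outcomes will be knee extensor strength and PBF". Table 1 and the Primary outcomes section also list both, but with PBF first, so the order of listing gives no consistent ranking.
- **Three arms.** "The final participants will be randomly assigned to an LRE-BFR, CRE or control group, with a 1:1:1 ratio".
- **Two post-baseline visits.** "Measurements will be performed at the baseline (week 0), end of the intervention (week 12) and follow up (week 24"; Table 1 marks both primary outcomes at weeks 12 and 24.
- **Analysis.** For comparisons between groups, the Statistical analysis section names one-way ANOVA or Kruskal–Wallis. For change over time: "Differences in the outcomes over time between the LRE-BFR, CRE and control groups will be analysed with linear mixed models".
- **Decision rule.** "The results will be described as 95% confidence intervals and regarded as significant at *P* < 0.05". No other threshold is given.
- **Sizing.** In the Sample size section, "the KES will be used as the primary outcome indicator to calculate the sample size", with alpha 0.05, power 0.8 and effect size f = 0.65, giving 27 participants before dropout and 33 after.

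**The concern.** The sample size treats the trial as having one decisive outcome tested at 0.05. The rest of the article gives it two, each read against the same 0.05, and does not say whether one success is enough or both are needed. If one is enough, the alpha in the sample size is not the error rate of the primary conclusion. The choice of headline outcome could also be made after the results are known. With 11 participants per arm, a chance finding on one of the two outcomes could become the trial's main message.

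**Working it through.** **Inputs from the article.** Two primary outcomes, three arms, two post-baseline visits, threshold 0.05, f = 0.65, 27 evaluable participants, 11 randomised per arm.

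**Assumed, because the article gives no figures.** Correlation of 0 to 0.5 between the two outcomes, and 0 to 0.8 between visits.

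**1. The plan's own figure.** Take the calculation to be a one-way ANOVA F test with three groups. The noncentrality is λ = f² × N = 0.4225 × 27 = 11.41, on 2 and 24 degrees of freedom. Power at alpha 0.05 is 0.817. With N = 24 it is 0.759, and 27 is the smallest total that reaches 0.80. The stated 27 therefore reproduces, with all of the 0.05 given to KES.

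**2. Error rate with one three-group test per primary outcome.** With no true effects and independent outcomes:

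1 - (1 - 0.05)² = 1 - 0.9025 = 9.75%.

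A null simulation (60,000 trials per setting, 9 or 11 per arm) gives 9.0% to 9.8% over the assumed outcome correlations. This step needs only two named primary outcomes, the stated threshold, and the reading that either may succeed.

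**3. Error rate if more tests were also treated as primary.** These come from the same simulation and are conditional, since the article does not spell out such tests.

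| Tests treated as primary | Chance of at least one false claim |
|---|---|
| Three-group tests, 2 outcomes × 2 visits | 14% to 19% |
| All pairwise, unadjusted, 2 outcomes, one visit (6 tests) | 21% to 23% |
| Each active arm against control, 2 outcomes × 2 visits (8 tests) | 24% to 31% |
| All pairwise, unadjusted, 2 outcomes × 2 visits (12 tests) | 31% to 40% |

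If pairwise tests follow only a significant three-group test for the same outcome and visit, the figure over both visits is again 14% to 19%.

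**4. Comparing remedies.**
- *Equal split of alpha (0.025 each).* Power for KES with 27 evaluable falls from 0.817 to 0.719. Restoring 80% takes 33 evaluable, and 33 / 0.8 = 41.25, so 42 randomised.
- *Fixed order of the two three-group tests.* If both null hypotheses are true, a false claim requires the KES test to reject, which has probability 5%. If only PBF is null, the PBF test itself limits the error to 5%. KES power stays at 0.817.
- *A looser version that fails.* Suppose a significant three-group KES test opened both the KES pairwise contrasts and the PBF test, each at 0.05. Let the two exercise arms be equal on KES but better than control, and let PBF be null. Simulation with 11 per arm and outcome correlation 0 to 0.5 gives a false claim rate of 8.6% to 9.3% at f = 0.65, and up to 9.9% with a larger KES effect. That is close to the inflation it was meant to remove.

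**The case against.** The strongest reply is that a journal article condenses a fuller plan. The decisive visit, the decisive contrast and any multiplicity adjustment may stand in a document not shown, so their absence here is not an error. That is fair, and the point does not rest on absence. It rests on what the article does fix: two outcomes of equal standing and one threshold for all results, against a sample size that gives the full alpha to one of them.

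A second reply is that KES is already favoured, since the article sizes on it and says why. This is true of the sizing, but a sizing choice is not a testing order, and PBF keeps its primary label throughout.

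A third is that requiring success on both outcomes would hold the error at or below 5%. That is correct, but the article does not state such a requirement.

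A reader might also infer that all 12 contrasts (2 outcomes × 3 pairs of arms × 2 visits) are primary tests, and so quote an error rate near 40%. The article does not support this. Its Statistical analysis section names three-group tests and a mixed model over time, with no unadjusted pairwise or visit-by-visit primary tests. The second objective, "to compare the efficacy of CRE and LRE-BFR and explore their potential mechanisms", implies a pairwise comparison but not how it is tested or whether it is adjusted. Nor do the outcomes labelled secondary belong in a count of false primary claims.

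**Conclusion.** The point holds at a false primary claim rate of about 9% to 10% against a nominal 5%. It assumes that success on either primary outcome is enough, that each outcome has one three-group test, and that the outcome correlation lies between 0 and 0.5. The 9.75% figure for independent outcomes needs no simulation. The larger figures, from 14% up to 40%, depend on further tests being treated as primary and on assumed correlations, so they should not be quoted as the plan's own error rate. The stated sample size reproduces and is not in question here. Severity: should fix. The inflation is about twofold, and a short statement made before the data are seen removes it.

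**What to change.** Amend the abstract, the Primary outcomes section and the Statistical analysis section to state the following:

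1. Week 12 is the primary time point.
2. The three-arm test of KES at week 12 is done first, at 0.05. The three-arm test of PBF at week 12 is done at 0.05 only if KES is significant.
3. Confirmatory claims are limited to these two tests. If pairwise claims are wanted, the named contrasts go into the same single sequence, and PBF is tested only after every KES contrast placed before it is significant.
4. Other pairwise contrasts, week 24 and the secondary outcomes are reported as supportive estimates with 95% confidence intervals.

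If a separate analysis plan already sets such an order, the article's wording should be brought into line with it.

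**Cost.** A few sentences, and no confirmatory PBF claim if KES fails. The KES alpha and the sample size are unchanged. The power of 0.817 belongs to the three-arm KES test, so any pairwise contrast added to the sequence would need its own power statement.

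### Two group comparisons are named without saying which decides, and neither is stated to include gender, age or baseline as covariates; the precision cost is large for one-way tests on follow-up values and modest for the mixed model

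*Protocol article*

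**What the plan says.** Under Randomisation and blinding, participants are "randomly assigned to an LRE-BFR, CRE or control group, with a 1:1:1 ratio", and the sequence is "stratified by gender and age to achieve a balanced distribution, with as many males and females in each group as possible". No age cut-point is given.

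Under Outcome measurements: "Measurements will be performed at the baseline (week 0), end of the intervention (week 12) and follow up (week 24"). Table 1 shows the same three times for both primary outcomes, percentage of body fat (PBF) and knee extensor strength (KES).

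The Statistical analysis section names two comparisons of the arms. Its first paragraph says that "comparisons between the groups will be conducted using one-way ANOVA or the Kruskal–Wallis test", with no time point, and follows this with 95% confidence intervals and a significance threshold of 0.05. Its second paragraph says that "Differences in the outcomes over time between the LRE-BFR, CRE and control groups will be analysed with linear mixed models following the intention-to-treat principle", and on dropout: "Missing data will be designated as randomly missing, and the data will be processed using maximum likelihood and linear mixed models". No covariates are listed for either approach, and neither is called primary.

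**The concern.** There are two problems.

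- **No decisive test.** Two methods are named for comparing the same three arms. In a trial of 33 people they can disagree, and a reader of the results could not tell which P value had been meant to count.
- **Precision.** Gender and age are balanced by design but are not stated to enter any analysis. The protocol's own figures suggest that gender matters: the PBF cut-offs are 35% for women and 25% for men, the handgrip cut-offs 18 and 28 kg, and the starting loads for the KES test 45% and 64% of body weight. One-way ANOVA and Kruskal–Wallis take no covariates. On follow-up values they leave stable differences between people, including those due to gender, in the error term. They also use only people observed at that visit, while the plan allows for 20% dropout.

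At 9 to 11 people per arm, interval width is the main limit on what the trial can conclude.

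**Working it through.** **Inputs from the protocol article.** Three arms, 1:1:1; alpha 0.05, power 0.80, effect size f = 0.65; 27 evaluable (9 per arm), 33 randomised (11 per arm); outcomes at weeks 0, 12 and 24.

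**Assumed, because the article gives neither.** The correlation ρ between baseline and follow-up (0.5 to 0.9), and the share of outcome variance due to gender (0 or 30%).

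**Step 1: the plan's own sample size.** For an unadjusted one-way ANOVA F test the noncentrality is N·f², with 2 and N − 3 degrees of freedom. N = 24 gives power 0.759 and N = 27 gives 0.817, so 27 is reproduced. For dropout, 27 × 1.2 = 32.4, rounded up to 33. The size therefore matches a one-way ANOVA without covariates.

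**Step 2: variance of a pairwise week-12 contrast, relative to follow-up values alone.**

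- Follow-up values only: 1
- Mixed model with week 0 as a response and free baseline means (complete data): equivalent to change from baseline, 2(1 − ρ)
- Baseline-adjusted: 1 − ρ²

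Ratio of standard errors to the baseline-adjusted analysis:

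| ρ | Follow-up only, 1/√(1 − ρ²) | Mixed model, √(2/(1 + ρ)) |
|---|---|---|
| 0.5 | 1.15 | 1.15 |
| 0.7 | 1.40 | 1.08 |
| 0.8 | 1.67 | 1.05 |
| 0.9 | 2.29 | 1.03 |

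**Step 3: 95% CI half-width at 9 per arm, in SD units.**

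- Follow-up only: t(24 df) × √(2/9) = 2.064 × 0.471 = 0.97.
- Mixed-model change contrast: 0.97 × √(2(1 − ρ)) = 0.97, 0.75 and 0.62 at ρ = 0.5, 0.7 and 0.8.
- Baseline-adjusted: t(23 df) × √(2/9) × √(1 − ρ²) = 0.84, 0.70 and 0.59. Simulation (3000 replicates), which also carries the small cost of estimating the baseline slope, gives about 0.85, 0.70 and 0.59.

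**Step 4: what gender adds.** Simulated half-widths with ρ = 0.7 and gender explaining 30% of variance:

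| Analysis | 9 per arm | 11 per arm |
|---|---|---|
| Follow-up only | 0.981 | 0.878 |
| Follow-up only + gender | 0.808 | 0.723 |
| Change | 0.742 | 0.671 |
| Change + gender | 0.743 | 0.672 |
| Baseline-adjusted | 0.700 | 0.628 |
| Baseline-adjusted + gender | 0.676 | 0.607 |

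A gender effect that is constant over time cancels from the change contrast. It matters for follow-up-only tests and adds a little after baseline adjustment.

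**Step 5: power at N = 27 for a more modest effect** (f = 0.4 on the follow-up-only scale, assumed; ρ = 0.7). Follow-up only gives 40%, the mixed-model change contrast 61%, and baseline adjustment 68%, both with one covariate and after spending two more degrees of freedom on gender and age.

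**The case against.** The strongest reply is that the one-way tests may not be meant for outcomes at follow-up. They stand beside the descriptive statistics and the chi-square test, ahead of a separate paragraph on outcomes over time, and intention-to-treat and maximum likelihood are attached to the mixed model. Comparing the arms at baseline is a natural reading. The article is also condensed, so a covariate list may sit in a full protocol or analysis plan that is not shown, and a mixed model without a baseline covariate is a valid analysis.

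Much of this stands. A reader might infer that the planned analyses use neither baseline nor strata and so give needlessly wide intervals throughout. The article does not support that. Week 0 is one of the three measurement times, so a model of outcomes over time would normally include it and already recovers most of the precision. Leaving gender out does not widen its change contrast (0.671 against 0.672 in step 4). Nor can it be said that the plan breaks its intention-to-treat principle: that would follow only if the one-way tests decided on follow-up data.

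The reply does not remove the ambiguity. Nothing limits the one-way tests to baseline, the significance threshold follows directly after them, and the sample size matches an unadjusted one-way ANOVA. No covariate list kept elsewhere could bring baseline or strata into tests that take no covariates.

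**Conclusion.** The point holds as a defect in how the analysis is fixed. Two group comparisons are named, neither is made decisive, and neither is stated to adjust for the stratification factors or for baseline as a covariate.

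Its size depends on which comparison carries the inference:

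- **One-way tests on follow-up values:** the loss is large. The half-width at 9 per arm is 0.97 SD, against about 0.85, 0.70 and 0.59 SD at ρ = 0.5, 0.7 and 0.8.
- **Mixed model with week 0 as a response:** the loss is modest. The standard error is about 15%, 8% and 5% larger than with baseline adjustment, and gender brings only a small further gain.

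These figures rest on assumed values of ρ and of the gender share of variance, on complete data, and on baseline means left free between arms in the mixed model. The article states none of these. The contrasts of 0.97 with 0.70 SD and of 40% with 68% power must not be read as the cost of the mixed model; against that model, at ρ = 0.7, the change is from 0.75 to 0.70 SD and from about 61% to 68% power.

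**What to change.** State one decisive analysis: a linear mixed model for weeks 12 and 24 in all randomised participants, with group, time, group × time, the baseline value of the outcome, gender and age as fixed effects, and the week-12 group contrast as primary. An equivalent form keeps week 0 as a response with baseline means constrained equal across arms, so that people with only a baseline value also stay in the likelihood. Enter age as a continuous variable.

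Limit one-way ANOVA and Kruskal–Wallis to describing the arms at baseline or to a labelled sensitivity analysis, and say which.

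The cost is a change of wording and about three degrees of freedom (baseline, gender, age). No extra participants or measurements are needed. With f = 0.65 and ρ = 0.7 at N = 27, adding gender and age to the baseline-adjusted analysis moves power only from 0.983 to 0.982, even if they explain nothing further.
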